## METHODS

**Interval walking training:** After day 1 the participants will engage in a three-month interval walking training program. An Interval-walking bout will consist of repeated cycles of 3 minutes of fast and 3 minutes of slow walking at 70% and 40% of the smart-phone assessed peak  $\text{VO}_2$ -rate, respectively. IWT is conducted for at least 60 minutes per day, three days per week. Compliance is monitored continuously using the on-board accelerometer logger.

**Estimation of  $\text{VO}_{2\max}$ :**  $\text{VO}_{2\max}$  will be assessed by employing a graded walking test protocol on a treadmill (Technogym Runrace, Gambettola, Italy). The test consists of a 5-min warm-up (individually determined moderate walking pace, 0% incline) followed by 2-min stages of increasing inclines (2% per stage) at individually determined brisk walking pace until the following criteria were met: plateauing of heart rate and  $\text{VO}_2$  with incremental workloads, respiratory exchange ratio  $> 1.1$  [6]. Oxygen consumption will be assessed using continuous indirect calorimetric measurements (CPET, Cosmed, Italy) and heart rate monitoring (Polar Electro, Holte, DK).

**Walking Economy:** To assess economy during fast walking, the steady-state oxygen consumption will be estimated during steady-state walking at a fixed speed on a treadmill. (Technogym Runrace, Gambettola, Italy). Measurements are made after a 15 minute customization period at 3 km/h. After the end of the period, measurements also are made over 5 minutes at the participants fastest self-selected pace to provide additional time for patients to reach steady-state oxygen consumption. The mean oxygen consumption of the later 2 minutes will be used. Oxygen consumption will be assessed using continuous indirect calorimetric measurements (CPET, Cosmed, Italy) and heart rate monitoring (Polar Electro, Holte, DK). The test will be performed at the same speed at all test days.

**Demographic Information:** Height, weight, waist and hip circumference will be measured by standard procedures. Dual x-ray absorptiometry (iDXA; Lunar, Madison, WI) will be used to assess whole body adiposity.

**Smart-phone administered  $\text{VO}_{2\text{peak}}$  test:** The test consists of four stages; 1) 30 seconds of standing still, 2) 2 minutes of slow walking, 3) 2 minutes of moderate walking at moderate intensity, 4) 2 minutes of walking at high intensity. The three later paces are self-selected. It is recommended that the phone is placed at the hips. However, it is likely that the phone might be placed at other body locations. Therefore the participant will be fitted with three phones; 1) at the hip, 2) hand-held and 3) on their upper-arm. Throughout the tests oxygen consumption will be monitored using continuous indirect calorimetric measurements (CPET, Cosmed, Italy) and heart rate monitoring (Polar Electro, Holte, DK). The test will be conducted as both a self-administered test and where the participants are paced during walking. To ensure test-retest reliability of the self-administered test, the participants perform two additional tests at home with two and four days apart from the second test day.

**Glucose Tolerance:** Following an overnight fast, an antecubital intravenous (i.v.) line will be placed and fasting plasma glucose, insulin, C-peptide, lipids, cytokines, and HbA1c will be determined. A standard 75 g oral glucose tolerance test (OGTT) will be performed over 2 hours with blood draws every 30 min for the measurement of glucose, insulin, and C-peptide.

**Resting Energy Expenditure (REE):** REE will be assessed via indirect calorimetry (Quark B2, Cosmed, Italy). REE will be assessed using a ventilated hood as described earlier [11].

## BIOLOGICAL MATERIAL

Blood will be collected in the study and stored in a research biobank throughout the study. This will be used to assess the potential differential changes in variables following the interventions. Approx. 100 mL blood will be collected per trial day. Total blood sampling will be approx. 300 mL. After the study termination the remaining biological material will anonymously get stored in a biobank for a maximum of 20 years and after that, it will be destroyed. If any later studies want to make use of the biological material, this will only take place following approval by the ethical committee. The biological material will not leave Denmark.

## STATISTICAL ANALYSES

Based on previous research it is assumed that the smartphone accelerometer output increases linearly until app. 9-10 km/h [12]. As it is not expected that our participant exceed this speed, backward stepwise *linear* regression analysis will be employed to develop an appropriate algorithm. In the full model we will include age, height, gender and monitor placement as co-variables. Log-likelihood test of the model fit will be employed to find the best fit to the data. Standard assumptions, such as linearity, independence between co-variables and normality of residuals will be checked. Bland-Altman blots will be used to assess the validity of the algorithm in an independent sample.

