The application is a free personal trainer individualizing IWT by employing the on-board accelerometer and global positioning system (GPS) to specify walking intensity and speed. Intensities are determined, as with the accelerometer-based training device with the option of including GPS determined walking speed. Data from the fitness test is logged on a server, and as the CPR-number is a part of the profile information on the application, it will enable researchers and clinicians to combine it with health information using the Danish registers. However, the validity of the  $VO_{2peak}$  test functions and sensitivity to exercise adaptation of smart-phone based tests are at large, unknown. As the DD2 are establishing a large cohort consisting of ~50.000 newly diagnosed T2D patients, a valid tool for assessing exercise capacity on a large scale is needed [8]. Moreover, if valid, this application provides clinicians and researchers with an easy and cheap tool to estimate physical fitness in clinic and in very large samples and not only in T2D patients.

The  $VO_{2peak}$  test is conducted by the patients using their smart-phones and it is based on three self-selected walking paces - slow, moderate and high. It is uncertain to which extent the self-selected walking paces are adequate to reflect a  $VO_{2peak}$ . Furthermore, as T2D patients have limited experience with exercise training, we speculate that acclimatization to high intense walking and pacing during the  $VO_{2peak}$  test can improve the validity.

The aim of the study is to validate the ability of the smart-phone based IWT application to accurately reflect physical fitness in a sample of T2D patients. More specifically we aim to;

- 1) Develop an algorithm for conversion of the  $VO_{2peak}$  test output to energy expenditure and validate the algorithm against maximal oxygen consumption in an independent sample. We hypothesize that the  $VO_{2peak}$  test algorithm will be a valid measure of physical fitness if the peak test is performed at a sufficient walking pace.
- 2) Investigate the effect of acclimatization to high speed walking on the ability of the patient to perform a valid  $VO_{2peak}$  test. We hypothesize that acclimatization will increase walking economy in

the patients thus increase the walking pace during the  $VO_{2peak}$  test without any increase in physical fitness.

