**Recruitment, information and informed consent:** Potential subjects are recruited through advertising on "www.forsogsperson.dk" and advertising in local health care centers. Potential subjects contact one of the project participants by telephone and are orally informed about the study. If no exclusion criteria are identified through the telephone interview, the written material and consent form is mailed to the participant with a free post envelope and he/she will be encouraged to read the information thoroughly. The potential participant is furthermore offered an information meeting, and the potential subject is informed about the possibility of inviting a private counselor to the information meeting. If the information meeting is requested, the study information will be given in a closed room where only the scientific participant, the potential subject and the potential private counselor will be present. If the potential subject is ready and wants to participate in the study, the study participant will be required to mail the informed consent form no earlier than 24 hours after the meeting. If the potential subject wants additional time to consider whether or not to participate in the study, an agreement about a telephone meeting after approx. one week is made. The subject will be informed of the possibility of contacting one of the scientific participants by telephone, in case of questions. If no additional oral information, besides the information provided initially by phone, is needed, the possible participant can return the consent form no earlier than 24 hours upon reception of the written material. Upon reception of the consent form by the scientific staff, the subject will be contacted by a member of the scientific staff and a date for the first visit is arranged.

**Study design:** The study is a validation study where the primary endpoint is  $VO_{2peak}$  and indirect calorimetry is used as reference to assess face validity of the InterWalk test. Data from all the study participants will serve a material for development of algorithms to predict  $VO_{2peak}$ . Data from the first and second lab day will form basis for a cross validation. Data from the third lab day will serve as material to

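### If acclimatization improves walking economy as Aim 2 expects, an equation with no visit check can report a false rise in VO2peak; calibration should be checked by visit

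*Protocol*

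**What the plan says.** Aim 1 (Protocol, Background) is to convert the phone "test output to energy expenditure and validate the algorithm against maximal oxygen consumption in an independent sample". The Statistical Analyses section gives the method: backward stepwise linear "regression analysis will be employed to develop an appropriate algorithm". On the model's content it says "In the full model we will include age, height, gender and monitor placement as co-variables". The linear form is justified because "it is assumed that the smartphone accelerometer output increases linearly until app. 9-10 km/h". Bland-Altman plots are planned in an independent sample, with no mention of visit.

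Aim 2 states "We hypothesize that acclimatization will increase walking economy in" the patients, and expects that pace will therefore rise in the smart-phone "test without any increase in physical fitness". Aim 3 asks whether change in the phone test reflects change in maximal oxygen consumption.

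On timing, Methods starts training after Day 1. Study Design says "Data from the first and second lab day will form basis for a cross validation" and gives Day 3 to the assessment of change. It says that all participants' data feed algorithm development, but not which days. For the phone tests, Methods adds "Throughout the tests oxygen consumption will be monitored using continuous indirect calorimetric measurements". Table 1 schedules phone tests on all three days and the graded VO2max test on Days 1 and 3.

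**The concern.** Better walking economy means less oxygen for the same speed. If phone output tracks speed, the oxygen cost per unit of phone output then falls between Day 1 and later days. An equation with one cost for all visits cannot follow that fall. A patient who walks faster at the same oxygen uptake produces more phone output, and the equation turns this into a higher estimated VO2peak.

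Aim 3 is exposed, because such a rise looks the same as the training effect that the phone test is meant to detect. If Days 1 and 2 are combined, the error takes opposite signs on the two days, and a Bland-Altman mean bias over both could be close to zero while the change between visits is wrong. App users outside the laboratory have no reference measurement that would show the difference.

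**Working it through.** **Figures in the plan.** The protocol gives no size for the economy change, so there is no figure of its own to reproduce on this point. Its development sample of 23 is not in dispute. An overall regression test with R² = 0.7² = 0.49, phone output plus four covariates as random predictors and alpha 0.05 needs about 22 by simulation (power 0.81). That is consistent with a calculation that makes no allowance for a visit term.

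**Inputs.**
- From the protocol: a linear equation, phone output linear in speed, the four covariates, training after Day 1, and Aim 2's unchanged fitness.
- Assumed: a fall e in net walking cost of 3%, 5% or 8% (10% in some illustrations); resting uptake of 3.5 ml/kg/min; peak uptake of 18, 24 or 30 ml/kg/min; and phone output at a given speed that does not change between visits.

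**Step 1: which situation produces a false rise.** Write VO2 = rest + c × output, and let c fall to c(1 − e).
- *Same pace, cheaper walking.* Output is unchanged, so the prediction is unchanged. The equation now over-predicts, but it shows no rise between visits.
- *Faster pace, same VO2.* Output becomes output/(1 − e). The prediction rises although VO2 does not. This is the situation Aim 2 describes.
- *Faster pace through more effort, cost unchanged.* Measured and predicted VO2 rise together, so the conversion is unbiased.

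**Step 2: size on net uptake.** False rise = 1/(1 − e) − 1 = e/(1 − e).
- e = 0.03: 0.03/0.97 = 3.1%
- e = 0.05: 0.05/0.95 = 5.3%
- e = 0.08: 0.08/0.92 = 8.7%

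**Step 3: size on total uptake.** Resting uptake does not drift, so the relative rise is [3.5 + (peak − 3.5)/(1 − e)]/peak − 1. For e = 0.05:
- peak 18: 14.5 × 0.0526/18 = 4.2%
- peak 24: 20.5 × 0.0526/24 = 4.5%
- peak 30: 26.5 × 0.0526/30 = 4.6%

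For e = 0.08 the same formula gives 7.0% to 7.7%.

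**Step 4: pooling Days 1 and 2.** With equal weight the pooled slope is c(1 − e/2). At e = 0.10:
- Day 1 error: 0.95/1 − 1 = −5.0%
- Day 2 error: 0.95/0.90 − 1 = +5.6%
- Mean of the two: about +0.3%
- Apparent change between days: 1/0.90 − 1 = +11.1%

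The mean bias almost vanishes and the false change is untouched.

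**Step 5: simulation.** The simulation had 25 patients and three paces per visit. Mean peak was 24 (SD 4), fast pace was 80% of reserve, and SD of cost was about 7%. The equation was fitted to Days 1 and 2 only.

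| Fall in cost | True gain in peak | Measured VO2 change, fast pace, Day 1 to Day 3 | One-slope equation | With output-by-visit term |
|---|---|---|---|---|
| 5% | 0 | about 0 | +4.1% | about 0 |
| 10% | 0 | about 0 | +8.5% | about 0 |
| 0 | 16% | +15.4% | +14.9% | +14.9% |
| 5% | 16% | +15.4% | +19.6% | +14.9% |
| 10% | 16% | +15.4% | +24.3% | +14.9% |

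The term removes the drift without Day 3 entering the fit.

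**The case against.** The strongest reply is that Aim 2 is a hypothesis under test and that the study measures what is needed to expose the problem. Oxygen uptake is recorded during the phone tests, economy is measured at a fixed speed on all test days, and VO2max is measured on Days 1 and 3, so drift would appear as disagreement with VO2max. Analyses by visit may also be in a statistical analysis plan that is not at hand. Much of this stands, and it keeps the point small. However, the full model is named in the protocol, and backward selection can only remove terms. Disagreement with VO2max would also not show by itself whether economy drift was the cause, and Table 1 lists no VO2max test on Day 2.

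It also stands that economy is oxygen per unit of speed. Equating it with oxygen per unit of phone output needs output at a given speed to be stable across visits, whereas the protocol assumes only linearity.

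Three stronger readings are tempting and are not supported:
- *That Aims 1 and 2 contradict each other.* The bias arises only if economy improves and pace rises for that reason. Aim 1 is itself conditional on a sufficient pace, and the Background speculates that acclimatization may improve validity.
- *That a known share of the training effect is conversion error.* Dividing the figures above by the 16% cited in the Background would suggest this, but the economy changes are assumed and the 16% comes from an earlier trial.
- *That the equation is derived from pooled Days 1 and 2.* The protocol ties those days to cross-validation and does not say which days feed the derivation.

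**Conclusion.** The point holds in conditional form. The named model and the single Bland-Altman check take no account of visit, while the protocol's own second hypothesis describes the situation in which that matters. Under assumed falls of 3% to 8% in net walking cost, the false rise is 3.1% to 8.7% of net oxygen uptake. On total uptake it is about 4.2% to 4.6% for a 5% fall. These figures rest on the assumed economy change, on pace rising at unchanged oxygen uptake, on stable phone output at a given speed and, for total uptake, on the assumed resting and peak values. If patients only walk harder, this bias is zero. The documents do not show that the drift will occur. They show that the planned analysis is not set up to tell it apart from a fitness gain. This is a cheap improvement, not a fault that invalidates the study.

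**What to change.** 1. State that Day 3 data stay out of the derivation, so that Day 3 remains a clean test of sensitivity to change.
2. In the derivation group, test an output-by-visit term, Day 1 against Day 2. Treat it as a diagnostic and not as an input to the app equation, since general users have no study visit to enter. Table 1 labels the Day 1 phone tests, but not those of Day 2, as free-living, so read any difference together with the fixed-speed economy results.
3. Report Bland-Altman bias of predicted against simultaneously measured oxygen uptake separately for Days 1, 2 and 3 and for the change between visits, alongside the planned Aim 3 comparison with VO2max.
4. If calibration differs by visit, state that unacclimatized and acclimatized tests are not interchangeable, and do not read the whole phone-test change as a fitness gain.

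The cost is one extra tested term beyond the four covariates in the sample-size calculation, and less precise visit-specific estimates with 25 patients per group. No new measurement is needed, because oxygen uptake is already to be recorded during the phone tests.

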## STUDY DESIGN

**Subjects, screening and sample size:** A total of  $n=50$  TD2 patients will be included in the study. All patients will undergo the protocol and intervention. However, 25 persons will be randomly chosen to act as a cross-validation reference group. Their data will act as reference to the developed algorithm. Based on previous studies on the association between  $VO_{2peak}$  and the maximal oxygen consumption ( $VO_{2max}$ ) we expect a correlation of 0.7. With a power of 0.8 ( $1-\beta$ ) and  $\alpha$  set at 0.05, allowing for four covariates we need a least 23 subjects undergo the study (group 1). With an *a priori* difference of 0.1 between the correlation coefficient ( $\rho^2$ ) in group 1 and the correlation coefficient in the independent sample (group 2) ( $\omega^2$ ), allowing for four covariates with we need 25 subjects in the cross-validation sample [9]. A medical examination, standard anthropometric measures, medical history, blood chemistry screen, ECG, oral glucose tolerance test (OGTT), Dual x-ray absorptiometry (DXA) scan, an assessment of walking economy, assessment of resting energy expenditure (REE), a smart-phone based  $VO_{2peak}$  test and a laboratory  $VO_{2max}$  test will be performed. If an individual meets the inclusion criteria, informed oral and written consent will be obtained prior to participation in the study, in accordance with guidelines developed by the ethical committees. For participants without a smart-phone the exercise and  $VO_{2peak}$  tests will administered on an iPod Touch.

**Inclusion Criterias:** T2D, age 30-70 y, BMI >18 but <40 kg/m^2 and confirmed T2D diagnose.

**Exclusion Criterias:** Pregnancy, smoking, contraindication to increased levels of physical activity [10], insulin dependence, evidence of thyroid, liver, lung, heart or kidney disease

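### The only validity method named for the independent sample, Bland-Altman plots of the full equation, cannot separate the phone's contribution from that of age, height and gender

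*Protocol*

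**What the plan says.** In the Protocol, STATISTICAL ANALYSES, the algorithm is developed by backward stepwise linear regression. On the covariates it says: "In the full model we will include age, height, gender and monitor placement as co-variables". A log-likelihood test is used to find the best-fitting model. The text does not say that the phone output must stay in the selected model. For validation it says: "Bland-Altman blots will be used to assess the validity of the algorithm in an independent sample". It gives no horizontal axis, no test of trend, and no comparison with an equation that leaves the phone out.

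In STUDY DESIGN (Subjects, screening and sample size), the planning rests on earlier studies of VO2peak and VO2max: "we expect a correlation of 0.7". With power 0.8, alpha 0.05 and four covariates, this leads to at least 23 patients for development. For the second group the protocol allows a "difference of 0.1 between the correlation coefficient" of the two groups and concludes that "we need 25 subjects in the cross-validation sample".

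The aims at the end of BACKGROUND are to validate the phone application as a measure of fitness (Aim 1) and to see whether it follows three-month change in maximal oxygen consumption (Aim 3).

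**The concern.** The study sets out to validate a phone test, but what is assessed in the independent sample is a composite equation. Age, height and gender can predict fitness without any phone. Good agreement of the composite therefore does not show that the phone signal is informative, and the named method has no step that would tell the two apart. According to FEASIBILITY, the results are to be implemented in the DD2, for which BACKGROUND foresees about 50,000 patients. If most of the agreement came from demographics, the test would look valid across patients and yet say little about change within a patient, because height and gender do not change over three months and age hardly does.

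A second, smaller matter is how the plot is read. Regression predictions vary less than the measured value, so a plot of difference against mean slopes even when the equation is correct.

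**Working it through.** **Inputs.** Correlation 0.7, so R² = 0.49; power 0.8; alpha 0.05; four covariates; 23 patients for development and 25 for cross-validation (STUDY DESIGN). The SD of VO2max is not given, so results are in SD units. The R² of age, height and gender alone is not given either; it is an assumption, varied below.

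**The plan's own figures.** The protocol does not name its sample-size formula.
- The closest match to 23 is an overall F test of R² = 0.49 with random predictors and five terms (phone output plus four covariates). It needs 22 patients (power 0.81), and 23 give 0.84.
- With four terms the same test needs 20. Fisher's z needs 14, or 18 after adding four.
- So 23 is approximately reproduced, and the nearest match treats 0.7 as a property of the whole equation.
- For the 25, simulation with four predictors fitted in 25 patients gives a probability of 0.77 that the loss in squared correlation is at most 0.1. No target probability is stated, so 25 is plausible but cannot be confirmed.

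**Limits of agreement.** For a calibrated prediction the error variance is (1 − R²) times the variance of VO2max, so the half-width is 1.96 × √(1 − R²) SD.

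| Model | R² | Half-width (SD of VO2max) |
|---|---|---|
| Full equation, as planned | 0.49 | 1.96 × √0.51 = 1.40 |
| No phone (assumed) | 0.49 | 1.40 |
| No phone (assumed) | 0.40 | 1.96 × √0.60 = 1.52 |
| No phone (assumed) | 0.30 | 1.96 × √0.70 = 1.64 |
| Everyone given the mean | 0 | 1.96 |

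The first row is the same whatever share of the 0.49 comes from the phone. Only a comparison with a no-phone row shows that share. These are values for known coefficients; estimating the equations in about 25 patients widens them.

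**Slope against the mean.** Write measured Y = P + e with Var(Y) = 1 and Var(P) = R². For D = P − Y and M = (P + Y)/2:
- Cov(D, M) = −(1 − R²)/2 = −0.255
- Var(M) = (1 + 3R²)/4 = 0.6175
- slope = −0.255/0.6175 = −0.413
- correlation = −√(0.51/2.47) = −0.454

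At ±1 SD of M the apparent bias is 0.413 × √0.6175 = 0.32 SD of VO2max. A 5% slope test in 25 patients would flag a perfectly calibrated equation in about 64% of studies (63% by Fisher's z; simulations 64 to 66%). For an equation estimated in 25 patients with four predictors it is about 46% (simulations 45 to 48%). Against the predicted value the rates are 5% and about 20% (19 to 21%); the excess in the second reflects genuine overfitting.

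**The case against.** A reader might infer that nothing in the study could show whether the phone adds anything. The document does not support that. The stepwise procedure with its log-likelihood test can test the phone term in the development data, although it is not specified for that purpose. Aim 3 is also a check that fixed demographics cannot pass. What remains is narrower: the independent sample has no such check.

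A reader might also infer that the main validity analysis would more likely than not report a false bias. The protocol states neither the axis nor a slope test, and an analysis plan that is not shown may settle both. The figure above one half needs a perfectly calibrated equation; for one estimated in 25 patients it is just under half. The mean difference and the limits of agreement are sound on either axis.

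Third, a phone of no value would reach the planned correlation only if demographics explained 49% of the variance. That is an assumption; at 30% they reach √0.30 = 0.55. The 0.7 is worded as an association between VO2peak and VO2max, so it is not certain that it describes the whole equation. If oxygen uptake from the separate walking stages enters the fit, demographics cannot explain differences between paces within a person. They can still contribute when the result is compared with one maximal value per patient, which is the stated reference.

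Finally, agreement of the complete algorithm with maximal oxygen consumption does answer Aim 1 as literally put, and the added value of the phone is a further question. That is fair, but the general aim is about the phone application, and a reader of the results will take the agreement as evidence for it.

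**Conclusion.** The point holds in a limited form. The one method named for the independent sample judges the whole equation, and its limits of agreement, ±1.40 SD at the planned correlation, are the same whether or not the phone contributes. How much this matters depends on the R² of demographics alone, which the documents do not give. Over an assumed 30% to 49%, the phone would narrow the limits by 0.24 SD (1.64 − 1.40) down to nothing. It is a gap in what the validation can show, and does not invalidate the study.

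The slope is a secondary caution about reading the plot. It applies only if the mean is used as the axis and the trend is taken as bias.

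**What to change.** 1. State that the phone output is kept in the selected model.
2. In the same development data, fit a model with age, height and gender but no phone output. Monitor placement has no role in it.
3. Report both models' mean difference, limits of agreement with confidence intervals and cross-validated r² side by side in the validation sample. Base the claim of phone validity on the improvement.
4. Plot differences against the predicted value, and report the calibration intercept and slope (measured on predicted).

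The cost is one extra regression and a few lines of text; no new measurements are needed. The phone's stated contribution may look smaller. With 25 patients the comparison will also be imprecise: the standard error of one limit is about 0.714 × √(3/25) = 0.25 SD, where 0.714 = √0.51. The improvement should therefore be given as an estimate with its interval, computed on the same patients for both models.
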